### Study sample

Adolescents are eligible for participation if they meet the following criteria: (1) age 12 to 23 years, (2) experiencing problems on multiple life domains (school, family, peers, leisure time), and (3) at risk for the development and progression of a deviant life style, such as predelinquents with antisocial behaviour, first time offenders and adolescents with mainly minor police contacts and offences (such as, purposely damage or destroy property, shop lifting and joyriding). Exclusion criteria are an IQ below 70, severe psychiatric problems, severe drugs-or alcohol use (dependency), absence of residence status in the Netherlands, and absence of motivation to stop committing criminal acts. NP-clients may be court-ordered, but are mainly referred by (primary or secondary) schools, social workers or they may be self-referred.

### Recruitment

The participants will be recruited via five locations of a large youth care institution in Amsterdam, the Netherlands. At the time of referral, adolescents and their parents will be informed about the NP-effectiveness study. After screening for the inclusion and exclusion criteria by clinical professionals at the youth care institution, adolescents are randomized to NP or to CAU. Immediately after randomization an appointment will be made in order to obtain written informed consent and to conduct the first assessment. The assessments will be carried out by junior researchers and master students (of Forensic Child and Youth Care Sciences). These students and researchers will be trained by means of a standardized protocol.

### Intervention

Youths in the experimental condition will receive the intervention New Perspectives (Elling & Melissen 2007), an intensive, short-term and community-based program targeting youth at risk for (persistent) juvenile delinquency. The main purpose of NP is to prevent or reduce delinquent behaviour and offending. Moreover, the program aims to improve the quality of life and addresses several key systems (home, school, peers and neighbourhood) in which the juvenile is embedded. The target group consists of at-risk youth from 12 to 23 years who are confronted with a sum of risk factors, in domains such as individual behaviour, family and friends, school/work, and neighbourhood. The NP program consists of an intensive coaching phase of 3 months followed by a 3-month aftercare phase. The total duration of the program is 24 weeks. Youth care workers, who have low caseloads, are available 24 hours a day, seven days per week. The average contact intensity per week is 8 hours per client. The following core activities and modalities are carried out by youth care workers: setting goals (in consultation with the client), coaching and confronting, motivational interviewing, empowerment and reinforcement of the social network (involvement of parents, peers, teachers, etc.), practical support, cognitive restructuring, problem-solving skills, and modelling (social workers act as role models) (Elling & Melissen 2007).

The control condition consists of care as usual (CAU), other existing standard services of youth care in Amsterdam. These services include child welfare services, such as family and/or individual counselling, social and/or cognitive behavioural skills training, academic service coaching, and mentoring.

### Data collection process

Adolescents and parents will complete self-report questionnaires using an online computer program at home. Both questionnaires have a login code to secure privacy. Youth will receive €20 and parents €10 per completed assessment. The youth care workers will fill out three questionnaires directly after the intensive intervention phase. The data will be treated as confidential: participants receive a unique code which is used for the online computer program and other research documents. Names are omitted and researchers declare that they will not provide any information of participants to third parties without their permission.

### Instruments

Table 1 shows the concepts, sources, and times of assessment for all used instruments. Most questionnaires will be administered at all measurement moments, except for the questionnaires of *intelligence*, *client satisfaction*, *motivation*, *therapeutic alliance* and *moral reasoning*. The questionnaires concerning treatment can only be filled out during the intervention phase (T2 en T3). The other two questionnaires (intelligence and moral reasoning) are filled out at one or two assessment moments in order to avoid overcharge of the respondents.

**Table 1 Tab1:** **Instruments at different assessments and informants**

Outcomes	Concept	Instrument	Items	Source			Assessment			
				A^1^	P^2^	S^3^	T1	T2	T3	T4
Primary	Delinquency	SRD	33	x			x	x	x	x
	Recidivism	Officialª								
Secondary	School/work situation	Official								
	Parenting behaviour	PBQ	30	x	x		x	x	x	x
	Parental monitoring	VTH	6	x	x		x	x	x	x
	Family functioning	VGFO	28		x		x	x	x	x
	Life events	VGFO	15		x		x	x	x	x
	Parental attachment	IPPA	12	x			x	x	x	x
	Peer affiliations	FFS	17	x			x	x	x	x
	Contact intensity peers	BVL	5	x			x	x	x	x
	Prosocial behaviour	PBQ	20	x			x	x	x	x
	Externalizing behaviour	SEV	72		x		x	x	x	x
	Substance dependency	CRAFFT	6	x			x	x	x	x
	Aggressive behaviour	BDHI-D	35	x			x	x	x	x
	Depressive behaviour	CDI-2	27	x			x	x	x	x
	Anxiety	SCAS	45	x			x	x	x	x
	Cognitive distortions	HIT	54	x			x	x	x	x
	Self-esteem	CBSA	5	x			x	x	x	x
	Moral reasoning	SRM-SF	11	x			x		x	
	Intelligence	GIT	40	x						x
	Social desirability	SDS	15	x			x	x	x	x
Treatment	Client satisfaction	C-toets	22	x				x	x	
	Motivation	VMB	12	x		x	x	x	x	
	Therapeutic alliance	TASC	12	x		x		x	x	
	Program integrity					x		x		
Moderators	Demographic factors	Gender	1	x	x		x			
		Ethnicity	1	x	x		x			
		Education	1	x	x		x			
		Income	1		x		x			
		Living	1	x			x			

^1^A = adolescent; ^2^P = parent; ^3^S = social worker; ªRecidivism: Official reports about arrests and reoffending of Policy Database for Judicial Documentation; School/work: Official reports of local government (DMO and DWI) about registration, truancy and drop-out.

### Primary outcome measures

The primary outcome measure is the presence of *delinquent behaviour* among adolescents*.* Participation, frequency and versatility in offending, will be assessed by the ‘Self-report Delinquency Scale’ (SRD) (Van der Laan et al. 2009; Van der Laan & Blom 2006). The SRD scale consists of 33 items divided in three types of delinquent behaviour: *violent crime*, *vandalism*, and *property crime*. The acts range in severity from vandalism and petty theft up to injuring someone with a knife or other weapon. First, for the 33 types of offending activities, participants will be asked if they had ever been involved in each of these acts. Examples of items are: “Have you ever wounded anyone with a knife or other weapon?” and “Have you ever covered walls, buses, or entryways with graffiti?” Next, for each of the acts, where respondents answer with “yes”, they are then asked how often they participated in diverse delinquent acts during the past 3 months. *Recidivism* will be assessed with data of the Research and Policy Database for Judicial Documentation. This database provides information on the number of arrests, type and severity of offence of adolescent’s reoffending during the research period.

### Secondary outcome measures

The present study is based on a broad range of secondary outcome measures. Information about the *school* and *work situation* will be assessed by using the database of the local government in Amsterdam (*Dienst Maatschappelijke Ontwikkeling*, DMO and *Dienst Werk en Inkomen*, DWI). These data provide information about registration, drop-out rates, and truancy.

Parenting Behaviour, in particular *warmth*, *responsiveness* (parental support), *explaining*, *autonomy* (authoritative control), *strictness* and *discipline* (restrictive control), will be assessed with the ‘Parenting Behaviour Questionnaire’ (PBQ) (Wissink et al. 2006). The PBQ is applicable for different ethnic groups and could be used for both parental and juvenile reports. *Parental monitoring* will be measured by the ‘Vragenlijst Toezicht Houden’ (VTH), the Dutch version of the parental monitoring scale of Brown and colleagues (1993). Adolescents fill out how much their parents know about who their friends are; how they spent their money; where they were after school; which place they went when they left home; what they did in their leisure time; and what grades they received at school. Family Functioning will be assessed by the ‘Vragenlijst Gezinsfunctioneren Ouders’ (Janssen & Veerman 2005) based on five scales: *basic care*, *parenting*, *social contacts*, *childhood experience*, and *partner relation. Life Events* of the family will be measured by the ‘Vragenlijst Meegemaakte Gebeurtenissen’ (VMG) (Veerman et al. 2003). This questionnaire is based on parental reports about 15 specific life events. Parents fill out the specific period of the life event and whether the life event was experienced *positive* or *negative* by their child. The *quality of parent-adolescent relationship* will be assessed by using the short Dutch validated version of the ‘Inventory of Parent and Peer Attachments’ (IPPA) (Buist et al. 2004; Gullone & Robinson 2005). This instrument is designed to assess the extent to which adolescents felt secure by measuring the adolescents’ *trust* in availability and sensitivity of the attachment figure, the quality of *communication* and the extent of *anger and alienation* in the relationship with the attachment figure.

Adolescents’ perceptions of peer affiliation will be measured by the Dutch version of the ‘Friends’ scale which is a part of the ‘Family, Friends & Self Scale’ (FFS) (Deković et al. 2004; Simpson & McBride 1992). Adolescents indicate how many of their friends participated in a variety of deviant behaviours (e.g., purposely damage or destroy property). Affiliation with prosocial peers is measured by items of the FFS concerning prosocial activities (e.g. *good grades* and *sport*). The intensity of contact with peers is measured by a subscale of the ‘Basic Peer Questionnaire’ (BVL) (Weerman & Smeenk 2005). Adolescents answer how often they spend time with their peers during the week and weekends.

*Prosocial behaviour* of adolescents will be assessed by the ‘Prosocial Behaviour Questionnaire’ (PBQ) (Weir & Duveen 1981). This questionnaire is designed to measure positive aspects of adolescent’s behaviour. *Aggressive behaviour* will be measured by the Dutch self-report validated version of the ‘Buss-Durkee Hostility Inventory’ (BDHI-D) (Lange et al. 1994). The BDHI (Buss & Durkee 1957) consists of two subscales ‘Overt Aggression’ (measuring the tendency to express verbal or physical aggression) and ‘Covert Aggression’ (determining the emotional and cognitive components: hostility, irritability, suspicion, and anger). *Externalizing Behaviour* will be measured by the ‘Sociaal-Emotionele Vragenlijst’ (Social Emotional Questionnaire, SEV) (Scholte & van der Ploeg 2007). The SEV is based on the core symptoms of behaviour problems classified in the DSM and ICD: *attention deficits* and *hyperactivity*, *oppositional defiant*, *conduct* and *aggressive behaviour*, *anxiety*, *depression*, and *autistic behaviour*. Parents report how often their child shows problem behaviour. *Substance abuse* and *dependency* of adolescents will be measured by the CRAFFT Substance Abuse Screening Test (Knight et al. 2002). The CRAFFT is a specialized self-report screen to address both alcohol and drug dependency (Winters & Kaminer 2008).

*Internalizing problems* will be measured by the ‘Child Depression Inventory-2’ (CDI-2) (Breat & Timbremont 2002) and the ‘Spence Children’s Anxiety Scale’ (SCAS) (Spence 1998). The CDI-2 is a revision of the CDI (Kovacs 1985) and was translated in Dutch. This questionnaire is designed for measuring *depressive symptoms* (based on DSM-IV) of adolescents in different settings (at school; in child youth care settings). Adolescents report how they felt in the last two weeks. The SCAS is based on the DSM-IV and measures following symptoms of anxiety: *generalized anxiety*, *separation anxiety*, *social phobia*, *panic disorder*, *agoraphobia*, *obsessive-compulsive disorder* , and *specific phobia* (Spence 1998; Scholing et al. 1999).

*Cognitive Distortions* of adolescents will be assessed using the Dutch validated version of the ‘How I Think Questionnaire’ (Dutch version: HID) (Gibbs et al. 2001; Nas et al. 2005). The HIT is based upon four-category typology of self-serving cognitive distortions: *self-centred attitude*, *blaming others*, *minimizing-mislabelling* (consequences of) *behaviour*, and *assuming the worst* (Barringa et al. 2000). *Self-esteem* or feelings of worth and satisfaction with self will be measured by using the ‘Competentie Belevingsschaal voor Adolescenten’ (CBSA) (Treffers et al. 2002). This questionnaire is a Dutch version of the global self-worth subscale from the ‘Self-Perception Profile for Adolescents’ (Harter 1982). *Sociomoral Reasoning* of adolescents will be assessed by the ‘Sociomoral Reflection Measure–Short Form’ (SRM-SF) (Basinger et al. 1995). The SRM-SF addresses sociomoral values about *contract and truth*, *affiliation*, *life*, *property* and *law*. Adolescents are asked to evaluate and justify the importance of each value. The justificatory answers are scored for stages of moral reasoning (based on Kohlberg’s immature-mature stages). *Social Desirability* will be measured by the ‘Marlowe-Crowne Social Desirability Scale’ (SDS) (Crowne & Marlowe 1960). The SDS assesses the tendency of respondents to give socially desirable answers. *Intelligence* of adolescents will be measured by the ‘Groninger Intelligentie Test 2’ (GIT-2) (Verhage 1965). Three subtests of the GIT-2 will be used to indicate the level of intelligence of adolescents, namely *reasoning/induction and deduction* (‘Matrijzen’, 20 items), *visualization* (‘Legkaarten’, 20 items), and *numbers* (‘Cijferen’).

*Satisfaction* with treatment will be measured with the ‘C-toets’ (Jurrius et al. 2007), which has been designed for evaluating the satisfaction about treatment results of adolescents and their parents. *Motivation* for treatment of adolescents will be measured by the ‘Vragenlijst Motivatie voor Behandeling’ (VMB) (Van Binsbergen 2003). This questionnaire is based on the *Stages of Change Theory* (Prochaska et al. 1992) and presents the process of behavioural change in different stages. The *Therapeutic Relationship* will be measured by the ‘Therapeutic Alliance Scales for Children’ (TASC) (Shirk & Saiz 1992). The TASC is based on dimensions of (1) the child’s affective experience of treatment and (2) the child’s collaboration with the tasks of treatment. There is a client- and therapist version of the TASC. *Treatment Integrity* will be assessed by process evaluations consisting of analyses of program documents and protocols, structured interviews with program directors and staff, and observations (site visits). Moreover, we will conduct assessments with clinic personnel (social workers) through a structured program evaluation checklist which is based on the core elements of the intervention.

### Potential moderators

Information on demographic characteristics will be collected by adding questions about gender, ethnicity, age, education level, family income and situation of living to the self-report questionnaires.

### Statistical analysis

Primary analyses will be performed according to the intention-to-treat principle (Montori & Guyatt 2001). The effect of the intervention with regard to the difference in official arrest rates (recidivism) between the experimental and control group will be examined using logistic regression analysis and survival analysis. The primary (involvement in delinquency, SRD) and secondary continuous measures will be analyzed with ANCOVA using the outcome measures at post-test and follow-up as dependent variables, treatment condition as factor and pre-test scores as covariates.

Moderator analyses will be conducted using two-way ANCOVA’s with the moderators and treatment condition as factors, to examine interaction effects. For each questionnaire, the effect size is computed as Cohen’s *d*, based on adjusted means and standard errors, with a positive sign indicating improvement in the NP group relative to the control group. Mediator effects will be analyzed using structural equation modelling.

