### Design

This study protocol will follow the CONSORT statement (Moher et al. 2010). The design of this study involves a randomized controlled clinical trial (RCT) in which NP will be compared to CAU. Data of adolescents and their parents will be collected at four points in time: prior to treatment (T1 pre-test assessment), after 3 months (T2 the intensive intervention phase), immediately after treatment (T3 post-test assessment, 6 months after T1, the aftercare phase), and 1 year after treatment (T4 follow-up 12 months after T3).

Adolescents aged 12 to 23, who meet the eligibility criteria of NP (these criteria are described in next section) will be randomly assigned to either NP or CAU. Random assignment per adolescent will be executed by the researcher (first author) using computer generated block randomization. The ratio of the randomization between NP and CAU is 1:1. See Figure 1 for the procedure’s flow chart.

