### Sample size

Power calculations indicated that 90 adolescents per condition (assuming an alpha of 0.05, 0.95 power, and a medium effect size, based on power calculations of G*Power (Faul et al. 2009)), are sufficient to detect a difference in problem behaviour at post-test. There is also sufficient power to perform moderator-analyses for different subgroups (Power > .80 to detect small effects for 2 to 8 groups). Therefore, a total of 180 adolescents and parents will be included.

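### The stated ANCOVA treats youths who share an NP worker as independent; if outcomes correlate within worker, its standard error is too small and its error rate exceeds 0.05

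*Protocol article*

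**What the plan says.** Under Statistical analysis, the SRD and the secondary continuous measures are compared at post-test and follow-up by ANCOVA with "treatment condition as factor and pre-test scores as covariates". No other term is named. Recidivism is assigned to logistic regression and survival analysis, and the terms of those models are not listed.

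Under Intervention, NP is delivered by people with ongoing responsibility for several clients: "Youth care workers, who have low caseloads, are available 24 hours a day, seven days per week". The dose is high: "The average contact intensity per week is 8 hours per client", in a programme of 24 weeks. The workers coach, confront and serve as role models. CAU is a mix of other existing services, and how its providers are shared among youths is not described.

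Under Design, adolescents are randomised individually, and "The ratio of the randomization between NP and CAU is 1:1". Under Sample size, "Power calculations indicated that 90 adolescents per condition" suffice, "assuming an alpha of 0.05, 0.95 power, and a medium effect size", and no allowance for clustering is mentioned.

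The Background expects the working relationship between youth and worker to bear strongly on results. Alliance and treatment integrity are both measured (Table 1 and Secondary outcome measures).

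**The concern.** Individual randomisation makes youths independent at entry. It does not keep them so once several are coached by the same person. Workers differ in skill, in the alliance they build and in fidelity to the programme, and each worker's contribution is shared by all of that worker's youths. The NP mean then carries between-worker variation that an ANCOVA on condition and pre-test counts as if it were spread over independent individuals.

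The clustering arises in NP and may be weaker or different in CAU, so it does not cancel from the comparison. At stake are the standard error, confidence interval and p-value for the SRD, a primary outcome, and for every secondary continuous outcome. A plan that expects worker-linked factors to affect outcomes sits uneasily with a model that sets the worker variance to zero.

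**Working it through.** **Inputs from the article.** 90 youths per arm, 1:1 allocation, alpha 0.05, power 0.95, medium effect, ANCOVA with condition and pre-test.

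**Assumed inputs.** A medium effect is read as d = 0.5. The sidedness of alpha is not stated. The worker ICC (for outcomes after adjustment for pre-test) and m, the number of trial youths per worker, are not given and are varied.

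**Step 1: the plan's own figure.** For a t-test with independent youths and d = 0.5:
- one-sided alpha 0.05: 88 per arm are needed, and power at 90 is 0.955 (normal approximation: 87 and 0.956);
- two-sided alpha 0.05: 105 per arm are needed, and power at 90 is 0.916 (normal approximation: 104 and 0.918). With ANCOVA, two-sided alpha gives 90 only if the pre-post correlation is about 0.37, which is not stated.

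Every variant that comes near 90 assumes independent youths. Sidedness is a separate matter and does not decide this point.

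**Step 2: standard error under clustering.** With residual variance s², the ANCOVA takes the variance of the difference as 2s²/90. If NP youths are clustered by worker, the NP mean has variance DE × s²/90, where DE = 1 + (m − 1) × ICC. With clustering in NP only:

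ratio of true to model variance = (DE + 1)/2

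actual two-sided alpha = 2 × [1 − Φ(1.96/√ratio)]

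If CAU is clustered to the same degree, the ratio is DE.

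Example, ICC 0.05 and m = 10: DE = 1 + 9 × 0.05 = 1.45; ratio = 2.45/2 = 1.225; true SE = √1.225 = 1.107 times the model SE; 1.96/1.107 = 1.771; alpha = 0.077.

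| ICC | m | DE | True SE / model SE, NP only | Alpha, NP only | Simulated alpha, NP only | Alpha, both arms |
|---|---|---|---|---|---|---|
| any | 1 | 1.00 | 1.000 | 0.050 | – | 0.050 |
| 0.01 | 3 | 1.02 | 1.005 | 0.051 | 0.049 | 0.052 |
| 0.05 | 3 | 1.10 | 1.025 | 0.056 | 0.056 | 0.062 |
| 0.05 | 5 | 1.20 | 1.049 | 0.062 | 0.060 | 0.074 |
| 0.05 | 10 | 1.45 | 1.107 | 0.077 | 0.077 | 0.104 |
| 0.10 | 10 | 1.90 | 1.204 | 0.104 | 0.111 | 0.155 |
| 0.20 | 10 | 2.80 | 1.378 | 0.155 | 0.159 | 0.242 |

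The simulation used 20,000 trials per row and an unadjusted t-test with 90 per arm. Its Monte Carlo error near 0.05 is √(0.05 × 0.95/20,000) ≈ 0.0015, so the ICC 0.01 row cannot be told apart from 0.05.

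**Step 3: real power at 90 per arm, clustering in NP only, d = 0.5, normal approximation.** The correct standard error is √[(DE + 1)/90] in SD units. At ICC 0.05 and m = 10 it is √(2.45/90) = 0.165. One-sided power is then Φ(0.5/0.165 − 1.645) = 0.917, against 0.956 without clustering. Two-sided power falls from 0.918 to 0.858. At ICC 0.05 and m = 5, one-sided power is 0.940; at ICC 0.10 and m = 10 it is 0.873. Multiplying the one-sided 87 per arm by the variance ratio gives 96 (ICC 0.05, m = 5), 107 (ICC 0.05, m = 10) and 127 (ICC 0.10, m = 10).

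**The case against.** **The size is unknown.** This stands. No ICC, number of workers or recruitment period is given. Low caseloads may mean many workers with few trial youths each, and at ICC 0.01 to 0.05 with m = 3 to 5 the error rate is only 0.051 to 0.062. On the other side, a low caseload limits clients at one time, not over the whole of recruitment, because a place can be refilled after the 24-week programme. So m can be neither taken as large nor shown to be small.

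**The full protocol or analysis plan may add a worker effect.** Possible, but the article does more than stay silent: it names the factor and the covariate of the ANCOVA, and a worker term would be a change to that model.

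**Treating workers as random is a choice of target.** Partly fair: a random worker effect supports inference to NP with other workers. But the Discussion wants results that help practitioners and policy makers choose which programmes to implement, which reaches beyond the particular workers in the trial. Measuring alliance and integrity is useful but does not correct a standard error.

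**Stronger readings that a reader might infer.**
- That omitting location also inflates the error rate. Participants are "recruited via five locations of a large youth care institution in Amsterdam, the Netherlands", but they are randomised individually, so a location effect common to both arms largely cancels from the difference, and leaving it out can even be conservative. The article does not say that NP is delivered separately by location.
- That the recidivism models ignore clustering. Their terms are not listed, so this cannot be concluded, and the calculations above do not cover those outcomes.
- That delivery is strictly one worker per youth by a small team. The article says neither, and round-the-clock availability is compatible with shared cover, which would blur the clusters.

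**Conclusion.** The point holds in conditional form and is confined to the printed ANCOVA and the NP worker. If the worker ICC is positive and workers coach more than one trial youth, the standard error of the NP-CAU difference is too small and the two-sided error rate exceeds 0.05. It would go too far to say that the error rate does exceed 0.05 by a known amount, because both quantities that set the amount are missing. Over the assumed range ICC 0.01 to 0.20 and m = 3 to 10, with clustering in NP only, it runs from about 0.051 to 0.155; central assumptions (ICC 0.05, m = 5 to 10) give 0.062 to 0.077. Equal clustering in CAU would raise these to 0.074 to 0.104, but nothing in the article establishes it. The change should be made because the plan itself expects worker-linked factors to matter and the remedy is cheap. It does not invalidate the design.

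**What to change.** 1. Record the worker ID for each youth in NP, and in CAU where a worker can be identified. Workers already complete questionnaires after the intensive phase, so linking an ID adds little. The article does not say whether this link is already kept.
2. Replace the ANCOVA for the SRD and other continuous outcomes with a partially nested mixed model: keep condition and pre-test, and add a random worker effect in NP, and in CAU where a worker treats more than one trial youth. Use small-sample degrees of freedom (Satterthwaite or Kenward-Roger). A youth with no shared worker forms a cluster of one, so all randomised youths stay in the intention-to-treat comparison.
3. Apply the same principle to recidivism as a sensitivity analysis, for example with worker-clustered standard errors or a random worker intercept.
4. State the ICC and youths per worker assumed for the "Power calculations indicated that 90 adolescents per condition", and report the observed values.

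Location may be added as a covariate, but this is optional and not part of the error claim.

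**Cost.** One ID field and a change of analysis wording; no change to intervention or assessments. Confidence intervals become somewhat wider and real power is lower than stated (Step 3 of the working). If workers are few, the worker variance will be estimated imprecisely. If the ICC is near zero, little is lost.

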The program effectiveness of NP is examined in terms of decreased *delinquent behaviour* and *improvements* in life domains of juveniles, such as school, peers, and parents. Moreover, the study is focused on outcomes that are not directly addressed by NP, but are considered as factors related to delinquent behaviour, such as parental monitoring (Crouter & Head 2002), cognitive distortions (Barringa et al. 2000), self-esteem (Donnellan et al. 2005), and moral reasoning (Stams et al. 2006; Van Vugt et al. 2011). Given that externalizing behaviour problems often co-occur with internalizing problems (Barker et al. 2010), we also examine program outcomes related to depression and anxiety. Another important question of present study is related to the intervention effects for specific subgroups of youngsters. The NP client population in Amsterdam is very diverse with respect to ethnic background, gender and age. NP is also divided in different modalities for younger (below 16 years; NP ‘Preventief’ and ‘NP Plus’) and older adolescents (from 16 years; NP). In this respect it is important to detect possible differential effects of NP for these subgroups. In social work research and practice, there is little consensus about the need for, and effectiveness of, ethnically, gender-and age-tailored treatment (Wilson et al. 2003; Zahn et al. 2009). Although research consistently demonstrates that female juvenile offending is associated with specific risk factors (i.e., different from those of male juvenile offending) (Hipwell & Loeber 2006), gender-non-specific programs were found to be equally effective in reducing recidivism for boys and girls (Zahn et al. 2009). Also, a large amount of studies revealed that migrant children are at increased risk of mental health problems and experience specific risks related to stress and feelings of alienation due to the migration process (Stevens & Vollebergh 2008). Despite these different risk factors, mainstream service programs were found to be equally effective for minority and white juvenile delinquents in the United States (Wilson et al. 2003). Moreover, it is well known that the extent and impact of risk factors changes with age. For instance, the influence of peers in the adolescent’s behaviour increases with age, while the impact of parental supervision decreases with age (Loeber et al. 2006; Van der Put et al. 2011). Consequently, well-founded empirical knowledge about differential effects of prevention programs for different subgroups is needed.

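### Age and gender are collected and treated as tied to delinquency risk, but the main ANCOVAs adjust for the pre-test alone and the recidivism models name no covariate

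*Protocol article*

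**What the plan says.** The Statistical analysis section of the protocol article sets out three kinds of model.

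- **Self-reported delinquency (SRD) and continuous secondary outcomes:** ANCOVA at post-test and follow-up, with "treatment condition as factor and pre-test scores as covariates".
- **Recidivism (official arrests):** logistic regression and survival analysis. No covariate is named.
- **Moderators:** separate two-way ANCOVAs with the moderator and condition as factors, to test interactions.

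Age and gender therefore appear only in the moderator models. The Potential moderators section lists both among the demographic questions put to participants, and age is also an eligibility criterion checked at screening.

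The Background treats both as relevant. It says that the extent and impact of risk factors change with age and that offending by girls has its own risk factors. It also ties the form of the programme to age: "NP is also divided in different modalities for younger (below 16 years", with another form from 16.

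The Discussion expects the active control condition to lower the observed effect. It says this will be countered by raising power, but names no means, and the total stays at 180.

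**The concern.** When an ANCOVA's covariates are listed, that list is the analysis. Here it leaves out two variables that the protocol gives reasons to think prognostic and already holds. If they explain outcome variance beyond the pre-test, the treatment effect is estimated less precisely than the data allow.

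Recidivism is the plainer gap. It is a primary outcome, and its models name not even a baseline score that could absorb part of any age or gender difference between the arms.

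The first assessment follows randomisation, so a baseline questionnaire score could in principle be affected by knowing the arm. Age and gender cannot be, which makes them safe covariates in this design.

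The stakes are modest: a somewhat wider confidence interval, and an estimate more exposed to chance differences in two visible characteristics. With a reduced effect expected and the sample size fixed, cheap precision is still worth having.

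**Working it through.** **Inputs from the article.** 90 per arm, 180 in total, 1:1 allocation; alpha 0.05, power 0.95 and a medium effect (Sample size). One pre-test covariate in the ANCOVA (Statistical analysis).

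**Assumptions, because the article gives no figure.** Medium effect taken as d = 0.5. Extra R² of age and gender, meaning the share of variance left after the pre-test that they explain: 0 to 0.15. Pre-post correlation 0.5 in the power illustration. No dropout.

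**1. The plan's own figure.** The article states: "Power calculations indicated that 90 adolescents per condition". With a two-sample t-test at d = 0.5, a one-sided alpha of 0.05 needs 88 per arm, and power at 90 is 0.955, so the figure reproduces. With a two-sided alpha, 105 per arm are needed and power at 90 is 0.916. The article does not state sidedness. That is a separate matter; the rest of this check uses a two-sided test.

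**2. Effect of two added covariates on the standard error.** With condition and pre-test, residual degrees of freedom are 180 − 3 = 177. Adding age (linear) and gender leaves 175. The expected ratio of standard errors, after to before, is approximately

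sqrt[(1 − R²) × 177/175].

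The equivalent number per arm is 90 divided by the square of that ratio.

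| Extra R² (assumed) | SE ratio | Change in SE | Equivalent n per arm |
|---|---|---|---|
| 0 | sqrt(1.0114) = 1.006 | +0.6% | 89.0 |
| 0.05 | sqrt(0.9609) = 0.980 | −2.0% | 93.7 |
| 0.10 | sqrt(0.9103) = 0.954 | −4.6% | 98.9 |
| 0.15 | sqrt(0.8597) = 0.927 | −7.3% | 104.7 |

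Break-even: 1 − 175/177 = 0.011. Below an extra R² of about 1% there is a slight loss, never more than about 0.6%.

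**3. What this means for power.** Noncentral t, two-sided 0.05, 90 per arm, pre-post correlation 0.5. The standardised effect is d / sqrt(1 − 0.5²), divided by the SE ratio above, on 175 degrees of freedom (177 for pre-test only).

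| d | Pre-test only | R² 0.05 | R² 0.10 | R² 0.15 |
|---|---|---|---|---|
| 0.5 | 0.971 | 0.976 | 0.981 | 0.986 |
| 0.3 (diluted effect, assumed) | 0.637 | 0.655 | 0.678 | 0.703 |

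The gain is about 0.5 to 1.5 points at d = 0.5 and about 2 to 7 points at d = 0.3.

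**4. Recidivism.** The formula in step 2 belongs to linear models and does not carry over to logistic or survival models. The article gives no arrest rate or event count, so no figure is offered for that outcome.

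**The case against.** The strongest reply is that nothing here is wrong. A pre-test-adjusted ANCOVA after 1:1 randomisation is a conventional and valid primary analysis, and chance imbalance does not bias it. The gain rests on a prognostic strength that the article does not give; the Background speaks of risk factors, not of variance remaining after the pre-test. The one-sentence account of the recidivism models may be filled in elsewhere. The moderator ANCOVAs will also produce models containing age or gender. All of this stands and limits the point to a minor one. It does not remove it: the ANCOVA covariate list is stated rather than left open, and the moderator models test interactions and do not supply the primary estimate.

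Three stronger readings are tempting, and the article does not support them.

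- **That allocation is unstratified.** The Design section says allocation is made "using computer generated block randomization" and names no strata, but silence in a condensed article does not show that there are none.
- **That location should be adjusted for.** Participants are "recruited via five locations of a large youth care institution in Amsterdam", but nothing says that outcomes differ between locations. Adding location would bring the cost to six degrees of freedom and raise the break-even R² to 1 − 171/177 = 0.034.
- **That imbalance in age band is likely.** For a characteristic held by half the sample, with 90 per arm and no stratification, the hypergeometric chance of a gap of 10 points or more is 0.18. That is possible, but not likely.

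**Conclusion.** The point holds as a minor improvement in efficiency and robustness. It is not a flaw in validity. The ANCOVAs are fixed with the pre-test as the only covariate and the recidivism models name none, while two safe variables that the protocol itself links to delinquency risk are used only to test interactions.

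For the ANCOVAs, the standard error would fall by about 2% to 7% if age and gender explain 5% to 15% of the variance left after the pre-test. That range is an assumption. Below about 1% the change costs a negligible amount. The size for recidivism cannot be worked out from the article.

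**What to change.** In the Statistical analysis section, prespecify age (continuous) and gender as main-effect covariates:

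- beside the pre-test score in the SRD and secondary ANCOVAs;
- in the logistic and survival models for recidivism;
- together with any factor by which allocation was actually stratified.

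Make the change before outcome data are seen. It takes about one line and no new data.

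The costs are two degrees of freedom in the ANCOVAs and a change in what the recidivism models estimate: the odds and hazard ratios become conditional on age and gender and should be reported as such.
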